# LIST OF ABBREVIATIONS AND RELEVANT DEFINITIONS

| **ABR** | General Assessment and Registration form (ABR form), the application form that is required for submission to the accredited Ethics Committee; in Dutch: Algemeen Beoordelings- en Registratieformulier (ABR-formulier) |
| --- | --- |
| **AE** | Adverse Event |
| **AR** | Adverse Reaction |
| **CA**  **CAT** | Competent Authority  Competency Assessment Tool |
| **CCMO**  **CME** | Central Committee on Research Involving Human Subjects; in Dutch: Centrale Commissie Mensgebonden Onderzoek  Complete mesocolic excision |
| **CV**  **DFS** | Curriculum Vitae  Disease free survival |
| **DSMB** | Data Safety Monitoring Board |
| **EU** | European Union |
| **EudraCT** | European drug regulatory affairs Clinical Trials |
| **GCP** | Good Clinical Practice |
| **GDPR** | General Data Protection Regulation; in Dutch: Algemene Verordening Gegevensbescherming (AVG) |
| **IB** | Investigator’s Brochure |
| **IC** | Informed Consent |
| **IMP** | Investigational Medicinal Product |
| **IMPD**  **IQR**  **LRHC** | Investigational Medicinal Product Dossier  Interquartile range  Laparoscopic Right Hemicolectomy |
| **METC**  **OS**  **PLCRC** | Medical research ethics committee (MREC); in Dutch: medisch-ethische toetsingscommissie (METC)  Overall survival  Prospective Dutch ColoRectal Cancer cohort; in Dutch: Prospectief Landelijk CRC cohort |
| **(S)AE**  **SD** | (Serious) Adverse Event  Standard deviation |
| **SPC** | Summary of Product Characteristics; in Dutch: officiële productinformatie IB1-tekst |
| **Sponsor** | The sponsor is the party that commissions the organisation or performance of the research, for example a pharmaceutical  company, academic hospital, scientific organisation or investigator. A party that provides funding for a study but does not commission it is not regarded as the sponsor, but referred to as a subsidising party. |
| **SUSAR** | Suspected Unexpected Serious Adverse Reaction |
| **UAVG** | Dutch Act on Implementation of the General Data Protection Regulation; in Dutch: Uitvoeringswet AVG |
| **WMO** | Medical Research Involving Human Subjects Act; in Dutch: Wet Medisch-wetenschappelijk Onderzoek met Mensen |

# SUMMARY

**Rationale:** Surgical procedures for gastrointestinal oncology intervention are inevitably highly variable amongst surgeons and centers. Although acceptable to a degree, a substantial proportion of this variability has a potential relevance for both short term clinical outcomes and long term survival. For patients with right-sided colon cancer, a laparoscopic right hemicolectomy (LRHC) is the surgical procedure to remove the cancer and locoregional lymph nodes. This surgical technique has evolved during the last decade with the introduction of the intracorporeal anastomosis, the Pfannenstiel extraction and the complete mesocolic excision (CME). The latter is a dissection technique in embryological planes with a central vascular ligation of the segmental branches at its origin, resulting in an optimal lymphadenectomy. Given the insights from recent studies showing a positive association between the quality of surgery and relevant clinical outcomes, there is a great need to reduce the interinstitutional and intersurgeon variability and to implement an optimized and standardized surgical technique for right-sided colon cancer in the Netherlands to improve short- and long-term clinical and oncological outcomes. This kind of implementation needs a consensus of the key elements of the procedure and a formative quality assessment of LRHC. Detailed objective assessment of the LRHC is currently not performed in clinical practice nor in surgical training. Quality assessment of LRHC has great potential to improve surgical training and furthermore, implementation of a standardized technique will ultimately lead to better quality of care for patients suffering from right-sided colon cancer.

**Objective**: The main objective of this study is to improve surgical outcomes for patients with right-sided colon cancer by a prospective sequential interventional cohort study that aims to standardize the surgical technique with subsequent controlled implementation after standardized review of the current practice in a nationwide multicenter setting.

**Study design:** Prospective interventional sequential cohort study.

**Study population:** Patients with planned laparoscopic or robot-assisted (extended) right hemicolectomy for colon cancer of the caecum, ascending colon or hepatic flexure.

**Intervention:** Implementation of the standardized right hemicolectomy with proctoring during a subsequent period with prospective inclusion of consecutive patients and the collection of surgical videos in all participating hospitals.

**Main study parameters/endpoints:** The primary endpoint is the 90-day morbidity according to the Clavien-Dindo classification system. The design will be a non-inferiority trial to ensure safety during the implementation of a new adapted surgical technique. Secondary endpoints include 90-day mortality, intraoperative complications (i.e. vascular injury), conversion rate, operative time, blood loss, validated assessment of the dissection plane, validated assessment of the level of vascular ligation, grading of the resection specimen, total lymph node count, number of resected positive lymph nodes, resection margins, completeness of mesocolic excision based on the one year postoperative CT imaging, locoregional recurrence, distant metastasis, three year disease free survival (DFS), five year overall survival (OS) and long term morbidity (incisional hernia, adhesion related small bowel obstruction, readmissions, reinterventions, anastomotic leakage).

# INTRODUCTION AND RATIONALE

Right-sided colon cancer, located in the caecum, ascending colon or hepatic flexure is most often treated with the laparoscopic (extended) right hemicolectomy (LRHC). The aim of this surgical procedure is to remove the right hemicolon with a radical resection of the tumor and an intact colic mesentery containing all draining lymph nodes, to restore bowel continuity, and to do so, with minimal morbidity. The quality of the LRHC is first of all determined by the correct plane of dissection and the extent of lymph node dissection according to oncological principles that provide an optimal locoregional control and staging information. Furthermore, the surgical quality can be reflected by patient relevant short- and long-term clinical outcomes [1-3].

Unlike treatment with medication, a surgical intervention might be highly variable amongst surgeons and centers. This variability has a potential relevance concerning the clinical and oncological outcomes. As can be expected, it is known that the learning curve of surgeons adapting a new technique without standardized training and an implementation program can result in adverse clinical outcomes, such as a higher conversion and complication rate [4]. Therefore, standardized surgical training and proctoring of a new surgical technique is associated with a decrease of the negative impact caused by the learning curve [5]. Additionally, standardization of surgical techniques and credentialing of surgeons were found to reduce the adjusted in-hospital mortality [6, 7]. Recently, a large cohort study identified that good technical surgical skills are associated with a better long-term survival of patients with colorectal cancer [8].

For right-sided colon cancer, substantial procedural variation is present [9, 10]. The most important changes to the LRHC techniques in the last decade are the intracorporeal anastomosis and the complete mesocolic excision (CME) technique. CME encompasses a dissection along embryological planes to create an intact envelope of mesocolic fascia with a central vascular ligation to include all the lymph nodes along the supplying segmental vessels [11-14]. A questionnaire amongst trainees in the Netherlands confirmed the presence of a high variability in the surgical technique for right hemicolectomy. There is a great need for a formative quality assessment of laparoscopic right hemicolectomy, given the insights from recent studies showing the association between quality of surgery and relevant clinical outcomes. Detailed objective assessment of the laparoscopic right hemicolectomy is currently not done in clinical practice nor in surgical training. Quality assessment of laparoscopic right hemicolectomy has great potential to improve surgeon training and implementation of a standardized technique will ultimately lead to better quality of care for patients with colon cancer.

# OBJECTIVES AND HYPOTHESIS

## Main study objective

The aim of this study proposal is to improve surgical outcomes for patients with right-sided colon cancer by a prospective sequential interventional cohort study that aims to standardize the laparoscopic right hemicolectomy technique with subsequent controlled implementation after standardized review of current practice in a nationwide multicenter setting.

## Other study objectives

- To evaluate current practice and variations in technique for laparoscopic right hemicolectomy in the Netherlands.

- To give an overview of the vascular anatomical variations pertinent to laparoscopic right hemicolectomy.

- To evaluate the association of each variation performed in laparoscopic right hemicolectomy with the short- and long-term clinical and oncological outcomes.

- To reach consensus for a standardized step wise technique for laparoscopic right hemicolectomy using the most recent insights in optimized colon cancer surgery from literature and the results from the assessment during the first phase of the study, according to the Delphi method.

- Development and validation of a Competency Assessment Tool (CAT) for the standardized right hemicolectomy using surgical full-length videos of the laparoscopic right hemicolectomy procedures and the steps as identified in the Delphi method.

- To train and implement the standardized surgical technique in centers in the Netherlands for patients with right-sided colon cancer.

- To evaluate the short- and long-term clinical and oncological outcomes of the cohort after training and compare these with the cohort before training, implementation and proctoring of the standardized technique.

## Hypothesis

The primary hypothesis of this study is that the implemented and standardized laparoscopic surgical technique for right-sided colon cancer will be safe without an increase in the 90 days postoperative morbidity (non-inferiority design).

The second hypothesis is that the quality of surgery, objectively assessed by competency assessment, is an important determinant for long-term clinical patient outcomes.

The clinical outcomes of the surgical technique to treat right-sided colon cancer will be improved by safely implementing a standardized method according to the latest evidence. Improvements in outcome measures that reflect the oncological quality of surgery, such as validated assessment of plane of dissection and vascular ligation, grading of the resection specimen, total lymph node count and number of resected positive lymph nodes and completeness of mesocolic excision based on postoperative CT imaging are expected. Eventually, it is hypothesized that the surrogate oncological endpoints will translate in reduction of local and distant recurrences and improved 5-year overall survival (OS) and 3-year disease free survival (DFS).

# STUDY DESIGN

The design of this trial is a multicenter prospective interventional sequential cohort study with a transition period in which implementation of the standardized technique is performed in the same centers after education and hands on training. Proctoring of the new technique will be provided during implementation. The second data evaluation of the clinical and oncological outcomes of the consecutive patient group will be collected in the group of patients after proctoring is finished, the so called consolidation phase. This study is primarily designed as a non-inferiority trial, based on short-term postoperative complications, with the aim of ultimate improvement of long-term oncological outcome. The accrual of both the control patients and the patients after implementation will be within the national Prospective Dutch ColoRectal Cancer cohort (PLCRC) with additional video analysis and image collection with additional informed consent. The primary endpoint is safety during implementation of a new technique. This is measured by 90-day morbidity with the Clavien-Dindo classification [15]. The assumption is that the perioperative morbidity (26% 30-day overall postoperative complication rate; as earlier published based on the DCRA database [16]) will not be increased by implementation of the new standardized technique with a non-inferiority margin of 7%, therefore not exceeding 33%.

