## Sample size calculation

Sample size calculation is performed with the aim to demonstrate safety with non-inferiority for the primary endpoint overall 90-day morbidity. If there is truly no difference between the standard and experimental treatment, then 1095 patients (365 patient in each of the three groups) are required to be 80% sure that the lower limit of a one-sided 95% confidence interval (or equivalently a 90% two-sided confidence interval) will be above the non-inferiority limit of 7%. Therefore, in the one group 365 patients will be included (control group) and in the other group 730 patients will be included (implementation and consolidation phase together).

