# METHODS

## Study parameters/endpoints

### Main study parameter/endpoint

The primary endpoint is the 90-day morbidity with Clavien-Dindo classification.

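### The 80% power is worked out from a 30-day complication rate although the endpoint is 90-day morbidity, and the 33% figure matches the 7-point margin only if controls run at exactly 26%

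*Protocol*

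**What the plan says.** Section 8.1.1 sets the endpoint: "The primary endpoint is the 90-day morbidity with Clavien-Dindo classification". Section 6.4 sizes the trial for "non-inferiority for the primary endpoint overall 90-day morbidity".

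The only planning rate in the protocol is in section 5, a "26% 30-day overall postoperative complication rate; as earlier published based on the DCRA database". The same sentence assumes that this rate will not rise, "with a non-inferiority margin of 7%, therefore not exceeding 33" per cent.

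Section 6.4 does not repeat a control rate. It starts from "If there is truly no difference between the standard and experimental treatment" and asks to be "80% sure that the lower limit of a one-sided 95% confidence interval (or equivalently a 90% two-sided confidence interval"). The requirement placed on that confidence limit is that it "will be above the non-inferiority limit of 7" per cent. The result is "then 1095 patients (365 patient in each of the three groups) are required", split as 365 controls against 730 implementation and consolidation patients combined.

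No section converts the 26% from 30 to 90 days or argues that it can be used as it stands. None says what becomes of the 33% if the control cohort's rate is not 26%.

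**The concern.** Two things look wrong, and both come from the same sentence in section 5.

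First, the planning rate and the endpoint cover different windows. The share of patients with any complication by day 90 is at least the share with one by day 30. For rates below 50%, a higher event rate means a larger variance and, with a fixed absolute margin and fixed numbers, less power. The 80% quoted in section 6.4 may therefore not apply to the endpoint the trial will analyse.

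Second, section 5 expresses the limit as an absolute rate (33%) and section 6.4 as a limit on a difference (7%). The two agree at one control rate only. If both stand in the final text and the control cohort does not come in at 26%, the protocol contains two thresholds that disagree.

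At stake are the accuracy of the power statement and the clarity of the safety criterion.

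**Working it through.** **Inputs.** Control rate p = 0.26, at 30 days (section 5). True difference 0, one-sided alpha 0.05, power 80%, limit 0.07, 365 against 730 (section 6.4).

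**Step 1: reproduce the plan's figure.** For non-inferiority of two proportions with equal true rates, unpooled normal approximation and two post-implementation patients per control:

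n(control) = (1.645 + 0.842)² × p(1 − p) × (1 + 1/2) / 0.07²

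With p = 0.26: 6.183 × 0.1924 × 1.5 / 0.0049 = 364.1, rounded up to 365. The other group is 2 × 365 = 730 and the total is 1095, exactly as stated. Two alternatives do not match: 1:1 allocation gives 486 per group, and one-sided 0.025 at 1:2 gives 463 controls. So 26% is the rate behind the sample size, although section 6.4 does not name it.

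**Step 2: power at other control rates, numbers kept at 365 and 730.**

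SE = √[p(1 − p)(1/365 + 1/730)]; power = Φ(0.07/SE − 1.645)

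Example, p = 0.30: SE = √(0.21 × 0.0041096) = 0.02938; 0.07/0.02938 = 2.383; 2.383 − 1.645 = 0.738; Φ(0.738) = 0.770.

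| Assumed 90-day rate, both groups | Power with 365/730 | Total N for 80% power at 1:2 |
|---|---|---|
| 20% | 86.1% | 909 |
| 26% | 80.1% | 1095 |
| 28% | 78.4% | 1146 |
| 30% | 77.0% | 1194 |
| 35% | 74.0% | 1293 |
| 40% | 72.0% | 1365 |
| 50% (largest variance) | 70.5% | 1422 |

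Every rate other than 26% is an assumption.

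**Step 3: compare the 33% with the 7-point limit.** The increase that 33% would leave room for is 33 minus the control rate: 13 points at 20%, 7 at 26%, 5 at 28%, 3 at 30%, 0 at 33%. It equals the margin at 26% only. The limit in section 6.4 stays at 7 points whatever the control rate.

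**The case against.** The strongest reply is that the margin is sound and the effect on power is ordinary. Section 6.4 compares a confidence limit with 7%, and that limit does not depend on the control rate. In section 5 the 33% follows as a consequence of an assumption, so it reads as the sum 26 + 7. Any trial with a binary endpoint is sensitive to its planning rate, and here the worst case is still about 70.5%. The direction is also open: the trial excludes ASA 4, cT4b, M1 and emergency cases, so its own rate could be lower than the registry's, and power would then be higher.

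Most of this stands. A reader might infer that 33% is a fixed ceiling, that it would replace the comparison with the control cohort, and that margin and power would both collapse. The protocol does not support that. No section makes 33% a decision rule, and sections 4.2, 7.1 and 8.2 all compare with the pre-implementation cohort. The shrinking allowances in step 3 show why the two expressions should not stand side by side. They do not describe a test the protocol contains.

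The point about exclusions carries limited weight either way, because the protocol does not say which patients the 26% covers. It is a reason to show rates on both sides of 26%.

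What the reply does not remove is the mismatch. Section 5 labels the rate as a 30-day rate, section 6.4 names a 90-day endpoint, and nothing connects them.

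**Conclusion.** The concern holds in a limited form. The sample size of 1095 rests on a 30-day rate, so the stated 80% power is not established for 90-day morbidity. On the criterion in section 6.4 the loss is gradual: about 3 points of power at a 90-day rate of 30%, 6 at 35%, 8 at 40%, and at most about 10 at 50%. If the trial's rate is below 26%, power is above 80%, for example about 86% at 20%.

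The 7-point margin itself is not undermined. The 33% is a by-product of the 26% assumption that is true at one control rate only, and it should not remain beside the limit on the difference.

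These results assume equal true rates in both groups, independent patients, the normal approximation that reproduces the plan's own figure, and full numbers of 365 and 730. That the 90-day rate is at least the 30-day rate holds within the same patients under the same definition of a complication. How this trial's population compares with the registry is unknown.

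**What to change.** In section 5, delete the 33% or mark it as an illustration for a 26% control rate. State there and in section 6.4 that the criterion is the confidence limit for the difference between post-implementation and the trial's own control cohort, set against +7 percentage points.

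In section 6.4, name the 26% as the planning rate. Either justify it as a proxy for the 90-day rate or replace it with a 90-day rate. The control cohort is enrolled first (section 8.2), so its observed 90-day rate is one possible source. The 7-point margin should stay as it is when the planning rate is updated.

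Replace the single 80% with power over a range of plausible 90-day rates, including some below 26%. The table above would serve: about 86% at 20% to 72% at 40%, with a floor near 70.5%.

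The cost is protocol wording and a power statement that becomes a range, possibly a less favourable one. No extra patients are needed.

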# STUDY POPULATION

## Population (base)

Patients with a planned laparoscopic or robot-assisted (extended) right hemicolectomy for colon cancer.

## Inclusion criteria

In order to be eligible to participate in this study, a subject must meet all of the following criteria:

- Planned laparoscopic or robot-assisted (extended) right hemicolectomy for colon cancer of the caecum, ascending colon, hepatic flexure or proximal transverse colon;
- Age above 18 years;
- Signed informed consent.

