# TREATMENT OF SUBJECTS

## Investigational treatment

The implementation of the standardized laparoscopic right hemicolectomy with proctoring with prospective inclusion of consecutive patients with collection of surgical videos in all participating hospitals will be investigated. This method will be compared with the laparoscopic right hemicolectomy performed by the same hospitals before the training and implementation of the standardized technique. The clinical outcomes will be collected using the DCRA database and the oncological outcomes will be collected by the surgeons, surgical registrars and/or trained research nurses in the participating centers.

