   3. Prospective inclusion of consecutive patients undergoing laparoscopic right hemicolectomy in the participating hospitals in three months.
2. **Delphi phase**: Development of Standard Laparoscopic Right Hemicolectomy: an (inter)national Delphi study
   1. Approaching specialists to participate in the Delphi method (from participating hospitals in step 1).
   2. Identification of crucial steps and measures according to literature and expert’s opinion (Delphi method).
   3. Documentation of steps and the order in which they need to be performed, development of a competency assessment tool (CAT).
3. **Training phase**: Skills center training facility
   1. Training the participating surgeons in the method of the standardized laparoscopic right hemicolectomy, as consented in the Delphi method.
4. **Implementation phase**: implementing the standardized laparoscopic right hemicolectomy with proctoring during another period with prospective inclusion of 365 consecutive patients (total duration of inclusion is 4 months, possibility to extend until maximum of 6 months). N=40+ centers; N=365 videos.
5. **Consolidation phase**: Collection of a third group of 365 consecutive patients with collection of surgical videos in all participating hospitals (total duration of inclusion is 4 months, possibility to extend until maximum of 6 months). N=40+ centers; N=365 videos.
   1. Rating videos.
   2. Comparing with pre-implementation performance based on outcome measures reflecting oncological quality of surgery, and 90-day clinical outcomes.
   3. Comparing with pre-implementation performance based on the long-term outcomes. (3-year DFS and 5-year OS).

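### Eligibility admits robot-assisted resections, but the primary hypothesis, comparator, Delphi standard and control-phase enrolment line name only laparoscopic surgery, so the operation covered by the safety claim is not fixed

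*Protocol*

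**What the plan says.** The population text admits both approaches. Section 6.2 reads "Planned laparoscopic or robot-assisted (extended) right hemicolectomy for colon cancer of the caecum, ascending colon, hepatic flexure or proximal transverse colon", and section 6.1 and the study-population line of the Summary agree. None of these is limited to a phase.

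The sections that define what is tested speak of laparoscopy:
- Primary hypothesis (4.3): "the implemented and standardized laparoscopic surgical technique for right-sided colon cancer will be safe".
- Comparator (7.1): "This method will be compared with the laparoscopic right hemicolectomy performed by the same hospitals before the training and implementation of the standardized technique".
- Delphi objective (4.2): "To reach consensus for a standardized step wise technique for laparoscopic right hemicolectomy". Section 8.2 describes the Delphi product in the same terms.
- Control-phase enrolment (8.2, step 1): "Prospective inclusion of consecutive patients undergoing laparoscopic right hemicolectomy in the participating hospitals in three months".

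Some text names no approach: the objective and intervention in the Summary, and the study design section (5). Nowhere does the protocol say whether robot-assisted cases are trained for, proctored and operated to the standard. It does not give their expected share.

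For the comparison itself, section 10 assigns the chi-square test to categorical outcomes between patient groups. It adds multivariable regression, without listed variables, to find factors independently associated with an outcome.

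**The concern.** Two questions have no single answer in the protocol.

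The first is which operation the non-inferiority claim covers. Under 6.2, robot-assisted patients operated on after training count in the post-implementation group. Under 4.3 and 7.1, the claim concerns the standardised laparoscopic operation.

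The second is who enters the control cohort. A site following 6.2 enrols robot-assisted controls. A site following the control-phase line in 8.2 literally enrols none.

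This matters because the cohorts are sequential and not randomised, so nothing in the design balances the operative platform across phases. If the share of robot-assisted surgery differs between control and later phases, and morbidity differs by platform, part of the before-after difference is a platform effect. Separately, if some post-training patients did not receive the standard at all, the pooled difference would understate any harm from it. Understating harm makes a non-inferiority conclusion easier to reach.

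**Working it through.** **Inputs from the protocol**
- Control rate 26% (section 5: "26% 30-day overall postoperative complication rate").
- Margin 7 points, ceiling 33% (section 5).
- One-sided 5% (section 6.4: "lower limit of a one-sided 95% confidence interval (or equivalently a 90% two-sided confidence interval").
- Power 80% (section 6.4: "are required to be 80% sure that").
- 365 control against 730 implementation plus consolidation (section 6.4).

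**Plan's own figure.** With unpooled variance, 1:2 allocation and no true difference:

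n control = (1.645 + 0.842)² × 0.26 × 0.74 × 1.5 / 0.07² = 364.1, rounded up to 365. This gives 365 + 730 = 1095, as stated. Power at 365/730 is 80.1%. Operative approach is not an input, so the total does not depend on this point.

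**Dilution scenario.** The following are assumptions, because the protocol gives neither: robot-assisted share r, equal in all phases; 26% control morbidity for both approaches; a true excess of 7 points in laparoscopic cases; no excess in robot-assisted cases. Then

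- pooled excess d = 0.07 × (1 − r)
- SE = √[0.26 × 0.74/365 + p(1 − p)/730], with p = 0.26 + d
- P(non-inferiority declared) = Φ[(0.07 − d)/SE − 1.645]

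| r | d (points) | SE | P(declared) |
|---|---|---|---|
| 0 | 7.0 | 0.0288 | 5.0% |
| 10% | 6.3 | 0.0288 | 8.1% |
| 20% | 5.6 | 0.0287 | 12.4% |
| 30% | 4.9 | 0.0286 | 18.1% |

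If robot-assisted cases follow the standard and carry the same excess, d = 7.0 for every r and the error stays at 5.0%.

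**Shift in case mix.** Assume the share moves from 10% in the control phase to 30% later, the programme acts equally on both approaches, and robot-assisted morbidity differs from laparoscopic morbidity by x points. The apparent difference is then the true difference plus x × (0.30 − 0.10). The same normal approximation gives:

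| x (robot-assisted minus laparoscopic) | Apparent difference if truth is 7 | P(declared) | Apparent difference if truth is 0 | P(declared) |
|---|---|---|---|---|
| −5 | 6.0 | 9.8% | −1.0 | 89.1% |
| −3 | 6.4 | 7.6% | −0.6 | 85.9% |
| 0 | 7.0 | 5.0% | 0 | 80.1% |
| +3 | 7.6 | 3.2% | +0.6 | 73.2% |
| +5 | 8.0 | 2.3% | +1.0 | 68.0% |

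The bias takes the sign of x when the share rises, and the opposite sign when the share falls.

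**Laparoscopic cases only, within the fixed 1095.** With no true difference, SE = 0.02812/√(1 − r) and power = Φ(0.07/SE − 1.645). This gives 76.3%, 72.0% and 66.9% at r = 10%, 20% and 30%, against 80.1% for all patients.

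**The case against.** The best defence is that the protocol uses laparoscopic as shorthand for minimally invasive surgery. The Summary's objective and intervention and the design section name no approach. The training objective in 4.2 refers simply to the standardised technique. Most elements listed for the standard in 8.2 (dissection plane, vascular ligation, anastomosis, extraction site) are not tied to one platform by their wording; only trocar number and position clearly suggest one. Section 8.2 also plans one video per patient in each inclusion phase, which fits a standard meant for everyone enrolled.

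This largely stands. A reader might infer that robot-assisted patients lie outside the tested technique, and that the trial is therefore tilted towards non-inferiority. The documents do not support that. No section exempts these patients from the standard, dilution needs an assumed share and an assumed zero effect, and a changing share can bias either way.

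It can also be said that eligibility is governed by 6.2 and not by a line in an outline. That line gives three months where the rest of 8.2 gives four, so it may simply be loosely drafted. A further defence is that stratification belongs in a statistical analysis plan that is not shown, and that section 10 already foresees multivariable analysis. These arguments reduce the weight of the point but do not settle it. The hypothesis, population and comparator are fixed in the protocol, they disagree there, and an analysis plan cannot decide by itself which operation was meant.

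Finally, if the target is the effect of the programme on all eligible patients, the all-patient comparison is the right primary one. That is accepted.

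**Conclusion.** The contradiction is real: eligibility covers two approaches, while the hypothesis, comparator, Delphi standard and control-phase enrolment line cover one. It should be corrected because the comparison is sequential, not randomised, and unadjusted in its stated test.

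The size and direction of any bias are unknown. Under the assumed move from a 10% to a 30% share with a 3 to 5 point morbidity difference by platform, the shift is 0.6 to 1.0 point in either direction. Dilution is only a possibility. It would raise false non-inferiority to about 8%, 12% and 18% at shares of 10%, 20% and 30% if robot-assisted cases did not receive the standard and had no excess. It would leave it at 5% if they received the standard and had the same excess. The protocol does not let a reader tell which case applies.

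The stated sample size is unaffected. Restricting the primary claim to laparoscopic patients is not justified by this evidence and would cost power.

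**What to change.** 1. Reconcile 4.2, 4.3, 7.1 and 8.2 with 6.2, so that the same approaches are enrolled in all three phases, including in the control-phase line.
2. State whether the standard, the Competency Assessment Tool and the training cover robot-assisted cases.
3. Keep the all-patient non-inferiority comparison as primary, but estimate the risk difference stratified by planned approach. Planned approach is known before surgery.
4. Report, for each phase, the number of patients and the 90-day morbidity by planned approach. Give the planned-laparoscopic comparison as a supportive analysis.

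The cost is protocol wording and slightly more analysis work; the total of 1095 does not change. The supportive comparison has lower power (about 76%, 72% and 67% at robot-assisted shares of 10%, 20% and 30%), so it should be labelled accordingly and should not replace the primary analysis.
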